## **Background**

A chronic subdural hematoma (cSDH) consists of an accumulation of blood and degraded blood products located between the dura and the brain. cSDH often expand over time causing progressive neurological symptoms due to brain compression. Symptoms include altered mental state, hemiparesis, headache and in severe cases loss of consciousness and even death. Chronic subdural hematomas mainly affect the elderly due to brain atrophy, an increased tendency to fall and a high prevalence of antithrombotic medications. The incidence of cSDH in individuals over 70 years is approximately 58 per 100 000 per year. This makes cSDH one of the most common conditions requiring neurosurgical treatment.

Symptomatic cSDH can in the majority of cases be treated by surgical evacuation, most often performed as surgical evacuation via one or more cranial burr holes. Results from previous studies, including a randomized controlled trial, have showed that post-operative drainage reduces the recurrence rate.

The surgical procedure can be combined with intraoperative irrigation of the subdural space, and although potential benefits with this technique have not yet been ascertained in a controlled manner, there is evidence in favour of intraoperative irrigation. Still, the recurrence of cSDH is a major clinical problem with an estimated recurrence frequency of 3-21.5% with closed-system drainage %.

The irrigation fluid temperature may have an impact on recurrence rates of cSDH, possibly due to negative effects on the coagulation when using fluid at room temperature. It is also plausible that irrigation fluid at body temperature may

increase the solubility of the cSDH, thereby facilitating evacuation. The use of body vs. room temperature irrigation fluid varies between neurosurgical departments, and possibly even between individual surgeons. When a poll on the neurosurgical networking site *www.neurosurgic.com* addressed this particular question, the result of 620 respondents showed that 57 % use irrigation fluid at body temperature and 40 % irrigation fluid at room temperature and 3 % did not use any intraoperative irrigation.

The aim of this multicenter randomised controlled study is to investigate whether irrigation fluid temperature influence clinical outcome and recurrence rates in cSDH.

## **Hypothesis**

The intraoperative use of irrigation fluid at body temperature results in lower recurrence rates when compared to irrigation fluid at room temperature. Consequently, the defined null hypothesis will be that there is no difference between the treatment groups.

### **Primary aim**

The primary aim is to investigate whether irrigation with body-temperature fluid reduces recurrence rates of cSDH compared to room-temperature fluid.

### **Secondary aims**

Secondary endpoints include health related quality of life, complication profile and frequency as well as mortality rate.

## **Methods**

### **Study design**

A multicentre randomised controlled trial (RCT) evaluating the use of irrigation fluid at body temperature, 37°C, versus irrigation fluid at room temperature in burr hole evacuation of cSDH. Except from random allocation of treatment between irrigation fluid temperatures the management of the participants will not differ from the current management of patients treated for cSDH. A 1:1 block randomization will be performed at each clinic.

Participating sites are the neurosurgical departments at Sahlgrenska University Hospital (Gothenburg, Sweden), Karolinska University Hospital (Stockholm, Sweden) and the Uppsala University Hospital (Uppsala, Sweden).

The primary endpoint of the study is the recurrence rate within a 6-month follow up period. Secondary endpoints include mortality rate, complication profile and frequency and health related quality of life at follow-up.

The study is registered in *clinicaltrials.gov* and reported according to the SPIRIT guidelines for reporting a RCT study protocol.  
Trials registration: ClinicalTrials.gov, NCT02757235. Registered 05/02/2016.

## **Study participants**

Patients diagnosed with cSDH, where surgical evacuation is indicated, will be screened for inclusion in the study.

### *Inclusion criteria*

- Patients with cSDH requiring burr hole evacuation
- Patients older than 18 years of age.

### *Exclusion criteria*

- cSDH requiring surgical treatment other than burr hole evacuation.
- cSDH in a patient with an intracranial arachnoidal cyst.
- cSDH in a patient with a CSF-shunt.
- Patients who have undergone intracranial surgery before.

Patients with bilateral cSDH will be treated with the same irrigation fluid modality on both sides, and analysed as a single study participant.

## **Informed consent**

Informed consent will be obtained by the attending neurosurgeon prior to surgery of the cSDH. If the patient is unable to give consent, consent will be sought from a close relative. Withdrawal from the study is possible at any time, in accordance with the latest version of the declaration of Helsinki 2013.

## **Baseline variables**

Variables will be documented in the case report form (CRF) preoperatively, intraoperatively and within 24 hours postoperatively by the attending neurosurgeon.

### Preoperative variables:

- Age, sex, limb weakness, Glasgow Coma Scale (GCS), disorientation, seizures, dysphasia, headache, gait disturbance, mid-line shift, maximal width of the hematoma on CT and presence of uni- or bilateral cSDH. Concomitant medication will also be recorded for aspirin, clopidogrel, warfarin and new oral anticoagulants (NOACs). Dexamethasone use will not be recorded since it is not used in the treatment of cSDH in Sweden.

### Intraoperative variables:

- Unilateral or bilateral surgery, general or local anaesthesia, duration of surgery, irrigation fluid volume

Postoperative variables (within 24 hours)

- GCS, limb weakness, disorientation, dysphasia, headache, convulsions, gait disturbance, duration of postoperative drainage

## **Surgical technique**

Current management of cSDH at all participating departments is burr hole evacuation with intraoperative irrigation followed by active subgaleal drainage as described by Gazerri et al.

The patient will undergo surgery in the supine position under general or local anaesthesia, and 1-2 burr holes are placed over the maximum width of the hematoma. The dura is opened in a cruciate fashion and coagulated by bipolar diathermia. The subdural space is irrigated with Ringer's lactate of either body- or room temperature according to the result of the randomization. For irrigation a 50 ml syringe and a soft catheter is used. When the irrigation fluid runs clear a subgaleal drainage is inserted over the burr hole and tunnelled away from the skin incision. The drainage is connected to a collection bag with active suction ensuring continuous drainage. The patient is kept in the supine position until the drainage is removed the day after surgery. If the surgeon decides that a drain cannot be safely inserted the patient will be excluded from the study, although this should be a rare event due to the subgaleal location of the drainage.

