## **Randomization and blinding**

A total of 600 opaque envelopes (200 for each participating centres) with sequential study numbers containing randomly assigned irrigation fluid temperatures will be prepared. Importantly, the envelopes are not transparent even under direct illumination and will be kept sealed until the patient is draped in the operation room. Also, the envelopes are interconnected so that it is impossible to open these in the wrong order by mistake or on purpose. The envelope will be opened at the time of surgery by the surgeon performing the procedure.

It will not be possible mask the treatment allocation from the treating surgeon, nevertheless measures will be taken to minimise bias.

1. The patient will not be informed of treatment allocation.
2. To minimize detection and selection bias the treatment allocation will not be documented in medical records.
3. The investigator performing the statistical analyses will be blinded to treatment assignment until the final analysis is completed.

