## **Data management and statistical analysis**

A statistician blinded for treatment assignments will perform the analysis according to the intention to treat principle.

The primary endpoint (rate of recurrences requiring surgery within 6 months) will be analysed using  $\chi^2$ -test for frequency comparison.

Secondary endpoints will be analysed using appropriate statistics. Categorical data will be compared using  $\chi^2$ -test or Fishers exact test. Normally distributed numerical data will be analysed using t-test and Mann Whitney U-test if skewed.

Data will be collected the CRF and on password protected computers. CRF and consent forms are stored in locked rooms at each department. Each study participant's documents are identified by the randomization number, ensuring confidentiality.

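### Excluding patients without a drain after randomisation and irrigation contradicts the intention-to-treat analysis and can bias the recurrence comparison

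*Protocol*

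**What the plan says.** Five statements in the Protocol bear on this point.

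- **Allocation (Randomization and blinding).** The envelopes "will be kept sealed until the patient is draped in the operation room". Then: "The envelope will be opened at the time of surgery by the surgeon performing the procedure".
- **Masking (same section).** "It will not be possible mask the treatment allocation from the treating surgeon".
- **Order of steps (Surgical technique).** The subdural space is irrigated with fluid "of either body- or room temperature according to the result of the randomization". The drain follows: "When the irrigation fluid runs clear a subgaleal drainage is inserted over the burr hole".
- **Exclusion (Surgical technique).** "If the surgeon decides that a drain cannot be safely inserted the patient will be excluded from the study", with the qualification "although this should be a rare event due to the subgaleal location of the drainage". No expected rate is given.
- **Analysis (Data management and statistical analysis).** "A statistician blinded for treatment assignments will perform the analysis according to the intention to treat principle". No modified population is defined.

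The no-drain rule does not appear under Exclusion criteria. Nothing in the Protocol says that patients excluded for this reason are still followed up or analysed.

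**The concern.** A patient cannot be both excluded from the study and analysed as randomised. The drain decision comes after allocation, after the allocated treatment has been given, and from a surgeon who knows the arm. Randomisation therefore no longer protects the set of patients who are compared.

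Bias in the primary endpoint needs two things: excluded patients whose recurrence risk differs from the rest, and exclusion that differs between arms. The first is plausible, because the Background cites evidence that post-operative drainage lowers recurrence. The second is possible but not shown. The Background and Discussion suggest that temperature acts through coagulation and the solubility of the hematoma, so the operative field after irrigation might differ by arm. The surgeon's knowledge of the allocation could also colour the judgement. The measures against bias listed under Randomization and blinding (patient not told, allocation kept out of medical records, blinded analyst) do not reach this decision.

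If excluded patients are not followed, their 6-month outcomes are lost, and no later analysis plan can restore them.

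**Working it through.** **1. Sequence.** Patient draped → envelope opened by the surgeon → irrigation at the allocated temperature → fluid clear → drain step → exclusion if no drain can be placed. The exclusion comes last, whereas the listed exclusion criteria describe the patient's condition and history.

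**2. The plan's own figure.** Under Sample size calculations the inputs are 5% versus 12% recurrence, significance level 0.05 and 80% power. The mean rate is (5% + 12%)/2 = 8.5%. For a two-sided test with pooled variance under the null:

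n = [1.960·√(2·0.085·0.915) + 0.842·√(0.05·0.95 + 0.12·0.88)]² / 0.07² = 247.98, rounded up to 248 per group.

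This matches the stated 248 per group and 496 in total. The sample size is not in question, and keeping all randomised patients leaves it unchanged.

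**3. Size of the possible bias.**

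From the Protocol: a target of 600 with 1:1 allocation, so 300 per arm, and the χ² test for the primary endpoint.

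Assumptions, not in the Protocol:
- no true effect, with 8.5% recurrence in both arms;
- a fraction f excluded from one arm only (the worst case for imbalance);
- recurrence r among the excluded of 20% or 30%.

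Recurrence left in the depleted arm is (0.085 − f·r)/(1 − f), and the spurious difference is 0.085 minus that value. For example, with f = 5% and r = 30%: (0.085 − 0.015)/0.95 = 7.37%, a difference of 1.1 points.

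The false-positive rate comes from exact enumeration of two binomials under the two-sided χ² test without continuity correction. The depleted arm has 300(1 − f) patients and the other arm has 300. With no exclusions the rate is 5.1%.

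| f in one arm | r | Rate left | Spurious difference (points) | False-positive rate |
|---|---|---|---|---|
| 2% | 30% | 8.06% | 0.4 | 5.3% |
| 5% | 30% | 7.37% | 1.1 | 8.0% |
| 10% | 30% | 6.11% | 2.4 | 18.9% |
| 2% | 20% | 8.26% | 0.2 | 5.0% |
| 5% | 20% | 7.89% | 0.6 | 5.9% |
| 10% | 20% | 7.22% | 1.3 | 8.6% |

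**4. Milder imbalance, r = 30%.**
- Excluding 2% versus 1% gives 8.06% versus 8.28%: a difference of 0.2 points and a false-positive rate of 5.0%.
- Excluding 5% versus 2.5% gives 7.37% versus 7.95%: a difference of 0.6 points and 5.8%.
- Excluding 2% from each arm gives no difference.

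**5. No link with prognosis.** If the excluded have the same risk as everyone else, the spurious difference is zero whatever the value of f.

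**The case against.** The strongest reply is that the effect will be negligible in practice. The Protocol expects the event to be rare and gives a reason: the drain is subgaleal, over the burr hole and outside the space being irrigated. That also weakens the idea that what irrigation did to the subdural space decides whether a drain can be placed. No passage ties drain placement to temperature. The larger figures need 5% or 10% of one arm to be excluded, which is hard to square with a rare event. At 2% the worst case moves the false-positive rate only from 5.1% to 5.3%.

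All of this stands. It limits the likely size but does not remove the contradiction, which exists at any frequency. The Protocol sets no rate and no cap.

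A second reply is that exclusion may mean only leaving the protocol treatment path, and that an analysis plan not shown could define the analysis set. The text does not say that follow-up or data are kept, and its plain reading is removal from the study. If retention was meant, one sentence settles it. An analysis plan can define a population but cannot supply outcomes that were never collected.

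A third reply is that duration of drainage is already recorded, so absence of a drain may be partly visible. This is fair, but no listed variable captures the reason.

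**Conclusion.** The concern holds. The exclusion under Surgical technique and the intention-to-treat statement under Data management and statistical analysis cannot both be followed as written, and no other passage resolves the conflict. It affects who counts in the primary analysis, so it should be corrected.

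This is a risk of bias and not a demonstrated one. It matters numerically only if exclusions reach several percent, fall unequally between arms and are related to recurrence risk. At about 2% or less, under the 20% and 30% risks assumed here, the effect is close to nil. At 5% to 10% in one arm alone, the spurious difference is 0.6 to 2.4 points and the false-positive rate 5.9% to 18.9%. The exclusion rate, the imbalance and the no-drain risk are all assumptions, because the Protocol gives none of them.

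**What to change.** Reconcile the two sections by replacing the exclusion sentence under Surgical technique with a rule on the analysis set:

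- Every patient whose envelope has been opened stays in the study, is followed for 6 months and is analysed in the allocated arm.
- Absence of a drain is recorded as a protocol deviation with its reason, and counts are reported by arm.
- If an analysis without these patients is wanted, it is labelled as supportive (per protocol) and does not replace the primary analysis.

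This concerns follow-up and analysis only and takes no view on when a drain should be placed.

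The cost is one sentence in the Protocol and one field on the case report form. A few undrained patients may dilute the effect slightly. The required 496 and the target of 600 stay as they are.

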## **Randomization and blinding**

A total of 600 opaque envelopes (200 for each participating centres) with sequential study numbers containing randomly assigned irrigation fluid temperatures will be prepared. Importantly, the envelopes are not transparent even under direct illumination and will be kept sealed until the patient is draped in the operation room. Also, the envelopes are interconnected so that it is impossible to open these in the wrong order by mistake or on purpose. The envelope will be opened at the time of surgery by the surgeon performing the procedure.

It will not be possible mask the treatment allocation from the treating surgeon, nevertheless measures will be taken to minimise bias.

1. The patient will not be informed of treatment allocation.
2. To minimize detection and selection bias the treatment allocation will not be documented in medical records.
3. The investigator performing the statistical analyses will be blinded to treatment assignment until the final analysis is completed.

## **Outcome measures**

1. Recurrence rate of same-sided cSDH requiring surgery within 6 months.

2. EuroQol 5D (version 3L)

EuroQol 5D-3L (EQ-5D 3L) is a generic measure of health related quality of life (HRQL). The questionnaire contains 5 questions addressing mobility, self-care, usual

activities, pain/discomfort and anxiety/depression. Each question can be answered with “no problem”, “slight problem” or “major problem”.

3. Complications within the follow up period will be assessed using the Landriel Ibanez classification system. This system grades complications in 4 grades (Grade 1: no invasive treatment required, Grade 2: invasive treatment required, but not ICU. Grade 3: invasive treatment required and ICU, Grade 4: death).

4. Mortality will be analyzed as overall survival 6 months post-treatment.

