## **Sample size calculations**

The total number of patients will be 496 (248 in each group, respectively) for a power of 80 %. The calculation is based on a retrospective pilot study performed at Sahlgrenska University Hospital, 2013-14, with a 5 % versus 12 % recurrence rate when comparing irrigation with body-temperature fluid versus room-temperature fluid, respectively. A p-value of < 0.05 is considered statistically significant. To compensate for a loss to follow-up, we aim to include a total of 600 patients. Each centre will recruit 200 study participants ensuring homogenous recruitment between the participating centres. Although we do not anticipate a large loss to follow-up regarding the primary endpoint, we believe that this may be the case for the secondary endpoints. Thus, we will mainly compensate for a loss to follow-up regarding the secondary outcome measures such as EQ-5D 3L.

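### As worded, a non-fatal complication that needs ICU care but no invasive treatment falls into Grade 1, below a procedure done on the ward

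*Protocol*

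**What the plan says.** Under Study design, the Protocol names the endpoint: "Secondary endpoints include mortality rate, complication profile and frequency and health related quality of life at follow-up". Secondary aims lists the same three items.

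Under Outcome measures, item 3, complications during follow-up are to be assessed with a published neurosurgical classification (reference 17). The text continues "This system grades complications in 4 grades" and defines them in brackets: "Grade 1: no invasive treatment required, Grade 2: invasive treatment required, but not ICU. Grade 3: invasive treatment required and ICU, Grade 4: death".

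The Protocol adds nothing to these definitions elsewhere. It does not say what counts as invasive, where ICU care without an invasive procedure belongs, or whether the bracketed text or the cited source prevails if they differ. Under Data management and statistical analysis, categorical secondary data are to be compared by chi-squared or Fisher's exact test. No particular comparison of grades is named.

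**The concern.** A severity scale should order cases consistently. Here ICU need is what separates Grade 3 from Grade 2, so the scale treats it as a mark of greater severity. It has no such role among complications treated without an invasive procedure. Someone managed in ICU with drugs and monitoring alone shares a grade with someone who needed no more than ward care, and ranks below someone who had a procedure on the ward.

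The endpoint includes a complication profile as well as a frequency, and the grades are the only measure of severity that the Protocol sets out for non-fatal complications. The interim analysis concentrates on mortality and recurrence. If the arms differed in ICU complications managed without a procedure, the grades would not show that difference as one of severity. The population is mainly elderly and complications are registered for six months, so medical complications of this kind are in scope.

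**Working it through.** The Protocol gives no figure for this point, so the check is to apply its definitions to every possible case.

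**Inputs** (all from Outcome measures, item 3)
- Grade 1: "Grade 1: no invasive treatment required". ICU is not mentioned.
- Grade 2: "Grade 2: invasive treatment required, but not ICU".
- Grade 3: "Grade 3: invasive treatment required and ICU".
- Grade 4: death.

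**Step 1. Non-fatal complications.** Two yes/no features give 2 × 2 = 4 combinations.

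| Invasive treatment | ICU | Definitions met | Grade |
|---|---|---|---|
| No | No | Grade 1 only | 1 |
| No | Yes | Grade 1 only | 1 |
| Yes | No | Grade 2 only | 2 |
| Yes | Yes | Grade 3 only | 3 |

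The second row is the problem. It cannot be Grade 2 or Grade 3, because both require invasive treatment.

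**Step 2. Effect of ICU need.** With invasive treatment, adding ICU need moves the grade from 2 to 3. Without invasive treatment, it moves the grade from 1 to 1. So ICU need counts in one half of the table and not in the other, and row 2 ranks below row 3.

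**Step 3. Fatal complications.** Each of the four combinations with death meets Grade 4. Each also meets one lower definition, so the scale works for deaths only if the highest grade is taken, which is the natural reading. Fatal cases are therefore outside the problem.

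**Step 4. What is changed and what is not.** In one arm, let g1 be the non-fatal complications with neither feature, g2 those that are invasive without ICU, g3 those that are invasive with ICU, g4 the deaths, and a the non-fatal ICU cases without invasive treatment.
- As worded: Grade 1 = g1 + a, Grade 3 = g3.
- If ICU need alone defined Grade 3: Grade 1 = g1, Grade 3 = g3 + a.
- Total under either rule: g1 + g2 + g3 + g4 + a. Frequency is unchanged.
- Grade 4 = g4 under either rule. Deaths are unchanged.

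Between arms, with d the difference in a, the wording moves d out of the Grade 3 difference and into the Grade 1 difference. If d = 0, the between-arm differences in counts at each grade are unchanged, and only the grade distribution within each arm shifts.

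**Step 5. Size.** The Protocol gives neither a nor any complication rate. From the text alone, a could be anything from none to all of the Grade 1 cases. It also depends on what is meant by invasive. If ventilation or invasive lines count, many ICU patients move to Grade 3 and a shrinks. If they do not count, a is larger.

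**Step 6. Other parts of the plan.** The sample size rests on recurrence of 5% versus 12%, the primary endpoint is reoperation for recurrence, and mortality is a separate outcome. None of these uses the grades.

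**The case against.** The strongest reply is that the cited classification governs grading and the brackets only summarise it. If the summary is faithful, the trial has chosen an established scale and the complaint is with that scale. If the summary is abbreviated, assessors using the source may grade correctly and no misgrading follows. This stands in part: the source is not at hand, so misgrading in practice is not shown, and the published scale should not be rewritten without looking at it. It does not dispose of the point. The Protocol states the grades as rules, three sites must apply them, and nothing says that the source overrides the brackets. Either the summary is faithful and the inconsistent order is real, or the Protocol misdescribes its own instrument. The sentence needs checking in both cases.

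A second reply is that ICU patients usually receive something invasive. That reduces the affected group but does not empty it. Because the term is undefined, sites could also grade the same case differently.

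Some stronger readings are tempting and are not supported:
- A reader might infer that serious complications in general end up in the lowest grade. Only non-fatal ICU cases without invasive treatment do. Fatal cases are Grade 4, and the Protocol does not describe Grade 1 as unimportant.
- A reader might cite convulsions as a recorded complication that would be misgraded. The Protocol lists them as a postoperative variable within 24 hours, recorded in its own right, and does not link them to ICU care.
- A reader might want to express the problem as lost power for severe complications. The Protocol gives no rates for this and names no comparison of Grades 3 and 4 combined. Deaths within such a group could not be misgraded in any case.
- A reader might infer bias in favour of one arm. The same wording applies to both arms, and nothing shows that these cases differ between them.

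**Conclusion.** The point holds in a limited form. Read as written, the grade definitions put non-fatal complications that need ICU care without invasive treatment in the lowest grade, below a procedure on the ward. The order of severity is inconsistent, and the complication profile is distorted to that extent. The effect is confined to the severity part of one secondary endpoint, and its size cannot be derived from the Protocol.

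The conclusion assumes that assessors apply the bracketed wording literally and that some ICU care does not count as invasive. It is worth correcting because the rule is explicit, the endpoint is a named one, and the correction is small if made before grading starts.

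**What to change.** 1. Check the bracketed definitions against the cited classification before any complication is graded.
2. If the source allows it, correct the sentence so that ICU care without an invasive procedure is not left in Grade 1 by default. One workable wording is: Grade 1, neither invasive treatment nor ICU care; Grade 2, invasive treatment without ICU care; Grade 3, ICU care required for the complication, with or without invasive treatment; Grade 4, death.
3. Define invasive, saying whether measures such as ventilation and invasive lines count.
4. Put identical wording in the CRF at all three sites.
5. If the cited scale itself places these cases in Grade 1, keep the scale and report non-fatal complications needing ICU care by arm as a separate count.

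**Cost.** The text change is one sentence plus a definition. ICU need must be recorded for every complication, whereas the present wording requires it only when treatment is invasive. Tying Grade 3 to ICU care required for the complication helps to keep out patients who are in ICU for another reason. If the final wording departs from the cited scale, the Protocol must say so, and comparison with other studies using that scale becomes less direct.
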